## **9.2 Subgroups**

The primary and secondary endpoints will be analyzed in prespecified subgroups defined by:

- gender;
- age;
- BMI;
- location of myocardial infarction;
- physical diagnostics;
- ECG characteristics;
- laboratory findings;
- CMR-imaging findings.

Furthermore, we will perform “per protocol” analyses restricted to compliant patients and who did not receive ‘open label’ anti-hyperglycaemic strategies for clinical reasons (e.g. developed diabetes during the study).

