### 3. **STUDY DESIGN**

This is a single-center, prospective, randomized double blind study. In total, 380 patients with a first acute MI will be included. All patients will be randomly assigned to receive metformin 500mg 2dd1 or placebo 2dd1 on top of standard medical care. The study will take place at the University Medical Center of Groningen, a center with experience in primary PCI of patients with acute MI and with access to emergency cardiac surgery.

CMR-imaging is performed to determine LVEF four months after PCI, a period in which the remodeling of the heart has completed. CMR is a well-recognized, validated, and highly reproducible technique. After long-term follow-up, metabolic, neurohormonal and novel markers, clinical endpoints, and left ventricular function will be assessed.

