### **9.1.3 Tertiary study outcome parameters**

- Glycometabolic state (fasting blood glucose, HbA1c, insulin, GLP-1, DPP-4), inflammatory state (CRP, high-sensitivity CRP, TNF-alpha, etc), renal function (hemoglobin, hematocrit, urinary albumin excretion, creatinin, urea, sMDRD), lipid and cholesterol spectrum (LDL, HDL, total cholesterol, triglycerides), levels of advanced glycation endproducts (AGEs) measured in blood and by skin autofluorescence, neurohormones (NT-proBNP, plasma renin activity, aldosterone, etc), and protein profiles (e.g. mRNA) will be determined before hospital discharge and at each outpatient clinic visit to investigate the relationship of these factors with the intervention. Furthermore, the impact of these factors on LVEF, cardiovascular endpoints, and heart failure will be determined.
- Infarct size, TEI, functional MRI, and local contractility will be determined using LGE CMR imaging at 4 months follow-up. The impact of infarct size and TEI on LVEF, cardiovascular endpoints, and heart failure will be determined.
- The presence of pathologic Q waves on the ECG will be monitored before hospital discharge and at each outpatient clinic visit.
- Echocardiographic parameters of systolic and diastolic function, and valvular functions during hospitalization and at 4 months follow-up.
- Body Mass Index will be measured before hospital discharge and at each outpatient clinic visit.

- Safety and serious adverse event monitoring, i.e. the prevalence of lactic acidosis and worsening renal failure will be monitored during hospital admission, before hospital discharge and at each outpatient clinic visit.

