### **9.3.6 Cardiac magnetic resonance imaging**

To determine LVEF, cardiac magnetic resonance imaging (CMR) will be performed. CMR examination will be performed on a 3 Tesla clinical scanner (3T Achieva, Philips, Best, the Netherlands) at the Neuro-imaging Center (general director: [name]) using a phased array cardiac receiver coil at 4 months after primary PCI. Electrocardiogram-gated images are acquired during repeated

breath-holds of approximately 10 seconds. LV function is determined with cine imaging, using a segmented steady state free precession pulse sequence in multiple short axis views every 10 mm covering the entire left ventricle. Typical in plane resolution was 1.6 x 1.9 mm^2, with slice thickness of 6.0 mm (repetition time/echo time = 3.2/1.6 ms, flip angle 60°, matrix 256 x 156, temporal resolution 35 - 50 ms). Late gadolinium-enhanced (LGE) images are acquired to determine infarct size and transmural extent of infarction. A 2D segmented inversion recovery gradient-echo pulse sequence will be used, 15 minutes after administration of a gadolinium-based contrast agent (Dotarem, Guerbet, Roissy, France) (0.2 mmol/kg), with slice locations identical to the cine images. Typical in plane resolution is 1.4 x 1.8 mm^2, with slice thickness of 6.0 mm (repetition time/echo time = 9.6/4.4 ms, flip angle 25°, matrix 256 x 166, triggering to every other heart beat). The inversion time will be set to null the signal of viable myocardium. All MRI data are sent anonymously to independent cardiologists, who are blinded for randomization status, for quality control and blinded analysis.

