#### 9.4 Study visits

The study visits are summarized in the study flow chart (chapter 4, page 21). All efforts will be made to perform study visits as scheduled. However, a 5-day margin will be allowed for visits T1 and T2, and a 10-day margin will be allowed for visits T3, T4 and T5. All study procedures will have to be performed during study visit as scheduled, with the exception of the CMR-scan. The CMR-scan may be performed 10 days before visit T3.

- During hospitalization (T0)
  - inclusion/exclusion;
  - primary PCI (see inclusion criteria);
  - verbal followed by written informed consent;
  - randomization;
  - dispense study drug;
  - NYHA heart failure score (see appendix, chapter 14)
  - medical history;
  - concomitant medication;
  - ECG;
  - echocardiography (diastolic function);
  - skin autofluorescence;
  - serious adverse events recording;
  - clinical examination (blood pressure, heart rate, length, weight,);

- laboratory analysis (pregnancy test for female patients of childbearing potential, regular hematology and biochemistry, plus glycometabolic state, inflammatory state, lipid and cholesterol spectrum, AGEs, renal function, and neurohormones);
- oral glucose tolerance test (OGTT);
- Visit 1 (T1) at 2 weeks:
  - concomitant medication;
  - NYHA heart failure score;
  - ECG;
  - serious adverse events recording;
  - clinical examination (blood pressure, heart rate, length, weight,);
  - laboratory analysis (pregnancy test for female patients of childbearing potential, regular hematology and biochemistry, plus glycometabolic state, inflammatory state, lipid and cholesterol spectrum, AGEs, renal function, and neurohormones).
- Visit 2 (T2) at 6-8 weeks:
  - concomitant medication;
  - dispense study medication;
  - NYHA heart failure score;
  - ECG;
  - serious adverse events recording;
  - clinical examination (blood pressure, heart rate, length, weight,);
  - laboratory analysis (pregnancy test for female patients of childbearing potential, regular hematology and biochemistry, plus glycometabolic state, inflammatory state, lipid and cholesterol spectrum, AGEs, renal function, and neurohormones).

- Visit 3 (T3) at 4 months:
  - concomitant medication;
  - stop study medication and record the amount of study drug received, dispensed, consumed or administered for drug accountability;
  - NYHA heart failure score;
  - ECG;
  - echocardiography (diastolic function);
  - skin autofluorescence;
  - CMR-scan (primary endpoint);

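### Section 9.2 prespecifies subgroups by CMR findings, but the only CMR described is the 4-month primary-endpoint scan, so treatment comparisons within those subgroups are not protected by randomisation

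*Protocol*

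**What the plan says.** Section 9.2 opens with "The primary and secondary endpoints will be analyzed in prespecified subgroups defined by" and gives eight items, the last of which is "CMR-imaging findings". It names no CMR variable, time point or cut-off.

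The timing of the scan is the same wherever the protocol describes it:

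- Section 3: "CMR-imaging is performed to determine LVEF four months after PCI".
- Section 9.3.6 describes the examination "using a phased array cardiac receiver coil at 4 months after primary PCI" and gives no other time.
- Section 9.4 lists it at visit T3 only, as "CMR-scan (primary endpoint". The one latitude is that "The CMR-scan may be performed 10 days before visit T3". T0 has ECG and echocardiography but no CMR, and T1, T2, T4 and T5 list none.
- Section 9.1.3: "Infarct size, TEI, functional MRI, and local contractility will be determined using LGE CMR imaging at 4 months follow-up".

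Section 5.1 has study drug started within 3 hours after PCI. Section 9.1.1 makes LVEF from the 4-month CMR the primary endpoint.

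**The concern.** A subgroup analysis asks whether the treatment effect differs between kinds of patient. The comparison inside each subgroup is randomised only if treatment could not have influenced who belongs to it. Here membership is decided by a scan taken after about four months on metformin or placebo. If metformin raises LVEF, some patients who would have fallen in the low-LVEF stratum on placebo move to the high stratum on metformin. The arms within each stratum then contain different patients.

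At stake is how the subgroup results would be read. A real and uniform benefit would look much smaller in every LVEF stratum. With an off-centre cut-off it would also look different between strata, which could pass for an interaction. Labelling the analysis as prespecified gives it more weight than it can carry.

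**Working it through.** **1. Which variables could define the subgroup.** Sections 9.1.1 and 9.1.3 draw LVEF, infarct size, transmural extent (TEI) and local contractility from the 4-month CMR. All are post-randomisation outcomes. Section 2.2 lists infarct size and TEI among the things on which metformin's impact is to be studied. No CMR value obtained before the first dose is described.

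**2. The plan's own figures.** Section 11.3.1 uses a difference of 3 and an SD of 9:

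- N = (1.96 + 0.84)² × 2 × 9²/3² = 7.84 × 18 = 141.1, stated as 141 per group and 282 in total.
- 282/(1 − 0.26) = 381, stated as 380.

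Both reproduce closely, and nothing below depends on the small differences.

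**3. Split on 4-month LVEF.** Take LVEF as normal with SD 9 and a true effect of 3 in every patient. The placebo mean is not in the protocol, so 53 is assumed, which puts metformin at 56. For cut-off c and a = (c − μ)/9:

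- mean below c = μ − 9 φ(a)/Φ(a)
- mean above c = μ + 9 φ(a)/(1 − Φ(a))

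| Cut-off | Stratum | Placebo | Metformin | Difference |
|---|---|---|---|---|
| 54.5 (pooled median) | below | 46.75 | 47.84 | 1.09 |
| 54.5 (pooled median) | above | 61.16 | 62.25 | 1.09 |
| 50 | below | 43.81 | 44.61 | 0.81 |
| 50 | above | 58.39 | 59.85 | 1.46 |
| 45 | below | 40.07 | 40.65 | 0.58 |
| 45 | above | 55.98 | 57.91 | 1.94 |

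The median-split result does not depend on the assumed mean. Simulation of 2,000,000 patients gave the same 1.09 in each half, with 43% of the low half and 57% of the high half on active drug. At a cut-off of 50, 36.9% of placebo but only 25.2% of metformin patients fall below. The effect missing from the strata has gone into that shift in membership.

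**4. Median split on 4-month infarct size.** The correlation ρ with LVEF and the drug's shift d in infarct size (in SD units) are both assumptions. With λ(k) = φ(k)/Φ(k), the within-stratum LVEF difference is the same in both halves:

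3 − 9|ρ| × [λ(−d/2) − λ(d/2)]

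At ρ = −0.7:

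- d = 0: 3.0
- d = 0.17: 2.3
- d = 0.33: 1.7
- d = 3/(9 × 0.7) = 0.48, the whole effect acting through infarct size: 3 − 6.3 × (0.955 − 0.653) = 1.1

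Over ρ from −0.3 to −0.9 and d from 0.17 to 0.33, the result runs from about 2.7 down to 1.3.

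**5. Patients without a scan.** The protocol expects 26% to have no CMR: 0.26 × 380 = about 99 patients. They cannot be placed in any CMR stratum. For LVEF they are missing anyway. For the clinical secondary endpoints they are an additional loss, and they include anyone who dies before the scan.

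**The case against.** The strongest reply is that little hangs on it. The primary analysis is intention-to-treat on 4-month LVEF in the whole population (sections 9.1.1 and 11.1). No subgroup result changes it, its significance level or the sample size. That stands, and it limits the severity.

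A second reply is that the statistical analysis plan may settle the details. That holds for most of the list but not for this item: no cut-off or choice of variable turns a 4-month scan into a baseline measurement. The flow chart is not available to us, but the written procedure and visit list agree and leave no room for an earlier CMR.

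A third reply is that infarct size may be unaffected by metformin, in which case the split does no harm. That is possible and is the upper end of the range above, but it cannot be taken as given when the plan sets out to study metformin's impact on infarct size. The losses shown there rest on assumed correlations and shifts. For clinical endpoints the stratifier is a post-randomisation variable rather than the endpoint itself.

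A reader might also infer three stronger things that the protocol does not support:

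- **That all the section 9.2 subgroups are invalid.** Gender, age and infarct location cannot be altered by the drug. For laboratory and ECG items, values from before the first dose exist (admission blood in section 7.2, the presentation ECG in section 9.3.3), and the choice of time point may properly be left to the analysis plan.
- **That a true benefit would vanish in every CMR stratum.** In these calculations it shrinks but stays positive.
- **That the per-protocol set removes patients because they developed diabetes.** The text restricts it to compliant patients who "did not receive ‘open label’ anti-hyperglycaemic strategies for clinical reasons (e.g. developed diabetes during the study"). The criterion is open-label treatment, with diabetes as the example reason. A secondary per-protocol set of that kind is conventional.

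**Conclusion.** The point holds for the CMR item alone. Followed as written, section 9.2 calls for treatment comparisons within strata formed by the primary outcome or by other outcomes of the same scan.

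For LVEF strata the bias is certain whenever the drug has an effect. Under normality with the protocol's SD of 9, a uniform effect of 3 points becomes about 1.1 in each half at the median. At 50 it becomes about 0.8 and 1.5, with the placebo mean of 53 assumed. For infarct-size strata the size is conditional: none if the drug leaves infarct size alone, and down to about 1.1 under full mediation at a correlation of −0.7.

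The main result of the trial is untouched. This is a defect that should be corrected, not one that threatens the primary conclusion.

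**What to change.** Delete the CMR item from the subgroup list in section 9.2. Use CMR findings only as outcomes, or in association or mediation analyses clearly labelled exploratory; section 9.1.3 already plans to relate infarct size and TEI to LVEF and clinical events. Add one sentence stating that all subgroup variables, laboratory and ECG included, are values obtained before the first dose of study drug. Make the change before unblinding.

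It is a change of wording only and needs no new data or patients. The cost is one exploratory subgroup whose within-stratum effects could not have been read as treatment effects.

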## **9.3 Study procedures**

### **9.3.1 Baseline characteristics and clinical outcome**

Baseline characteristics that will be collected include age, gender, time of symptom onset of first and last symptoms, time of admission, history of CABG, previous PCI, stroke and MI, positive family history for cardiovascular diseases, existence of diabetes, hypertension, smoking status, heart rate,

systolic and diastolic blood pressure, weight and length. Current treatment at admission of the patients to the hospital will be recorded.

Death, reinfarction, and ischemia driven target vessel revascularization will be recorded at 30 days and at 4 months and after long-term follow-up. Follow-up information will be obtained from hospital records, written correspondence and/or telephone interviews with the patient.

### **9.3.2 Coronary angiography**

A coronary angiogram will be obtained at baseline. PCI of the ischemia related artery will be performed if indicated according to current protocols (possibly thrombus aspiration, balloon angioplasty and/or stenting, using bare metal stents or drug eluting stents). After the PCI procedure, a control coronary angiogram will be performed. Intravenously administered nitroglycerine will be given after the procedure and before the last angiogram in all patients.

The following baseline and post-procedural angiographic features will be recorded: Quantitative Coronary Angiography (QCA) data (reference diameter, minimal lumen diameter, and diameter stenosis, lesion length), the presence of thrombus, Thrombolysis In Myocardial Infarction (TIMI) flow grades, myocardial blush grade (MBG), and the presence of distal embolization.

QCA data and TIMI flow grades will be measured as previously described (72;73). The evaluation of MBG will be performed as described by Van 't Hof et al: 0, no myocardial blush; 1, minimal myocardial blush or contrast density; 2, moderate myocardial blush or contrast density, but less than that obtained during angiography of a contra- or ipsilateral non-infarct related coronary artery; and 3, normal myocardial blush or contrast density, comparable with that obtained during angiography of a contra- or ipsilateral non -ischemia-related coronary artery (74). Persisting myocardial blush ("staining") suggests leakage of contrast medium into the extravascular space and is graded 0. Next too MBG evaluation by the interventional cardiologist, MBG may also be assessed using the

Quantifying Blush Evaluator (QuBE), a computer program. QuBE has been demonstrated to provide practical, freely available, computer assessment of myocardial perfusion (75).

### 9.3.3 Electrocardiography

A standard 12-lead electrocardiogram is acquired at the time of presentation, after the PCI procedure, before hospital discharge, and at each outpatient clinic visit. Mean time interval between pre and post intervention will be registered. The ECG was recorded at a speed of 25 mm/s and a voltage of 10mm/mV. Q and R durations were measured in milliseconds along the PR baseline (1mm = 40ms), and the R amplitude in millivolts (1mm = 0.1 mV). Pre-intervention ECG will be analyzed on the presence of ST-deviation. The post-intervention ECG will be used to score the incidence and location of new Q-waves.

Electrocardiographic criteria of sufficient duration and amplitude for pathologic Q-waves were to meet the lead-specific standards of the Minnesota Code (codes 1-1 through 1-2, except 1-2-8) [Minnesota]. Additionally, the following criteria were used: Q wave  $\geq 30$ ms on lead aVF, Q wave  $\geq 30$  ms on leads I and aVL, Q wave  $\geq 30$  ms in  $\geq 2$  on leads V4 to V6, R wave  $\geq 40$  ms in lead V1, any Q wave in lead V2, and R wave  $\leq 0.1$  mV and  $\leq 10$  ms on lead V2 according to Selvester's QRS screening criteria for Q-wave myocardial infarction.

Two observers blinded to study randomization will analyze all ECG recordings.

### 9.3.4 Laboratory analysis

Laboratory testing is subdivided in standard (according to current guidelines) laboratory tests, which are commonly assessed for standard patient care, and additional laboratory tests. These additional tests include markers of inflammation and fibrosis, glycometabolic state, thrombogenic state, and

markers of heart failure. An overview of the laboratory analysis is added as an attachment (in Dutch). Enzymatic infarct size and glycometabolic state are discussed separately.

#### **9.3.4.1 Enzymatic infarct size**

Infarct size will be estimated by serial measurements of cardiac markers in serum, including creatinin kinase (CK), myocardial band fraction of CK (CK-MB), lactate dehydrogenase (LDH), and troponin T. The first measurement is taken as soon as possible after admission. Thereafter, frequent marker determinations are performed according to a schedule that calls for 4 to 6 measurements in the first 24-36 hours. To accommodate the problem in practice that exact predefined times for blood sampling are not always followed, the actual times of sampling, expressed as minutes after the moment of randomization, are recorded. To allow optimal comparison of the time courses of marker levels and to best approximate the area under the marker level curves, we use a dedicated algorithm (76;77). Per patient the algorithm interpolates the marker levels based on the precise time of measurement. Next, it determines for each of the predefined intervals if an actual measurement has been performed in that interval. Marker levels are determined on a Hitachi 717 automatic analyzer according to the International Federation of Clinical Chemistry (IFCC) recommendation, at 30 degrees Celsius. A peak marker release above the 75% percentile (i.e. the highest quartile) is defined as high enzyme release. Time to peak release is also determined.

#### **9.3.4.2 Glycometabolic state**

Patients with known diabetes are those reporting on an established diagnosis or those on glucose lowering medication, and will be excluded per protocol. The study protocol asks for fasting plasma glucose and glycosylated hemoglobin in patients with unknown glycometabolic state. The glycometabolic classification, performed at hospitalization, in normal glucose regulation, impaired glucose regulation (impaired fasting glucose and/or impaired glucose tolerance), and newly detected diabetes will be based on fasting plasma glucose and glycosylated hemoglobin according to

definitions in the guidelines. In addition, an oral glucose tolerance test (OGTT) will be performed to detect the sensitivity for glucose administration.

If diabetes or prediabetes is diagnosed, according to the current guidelines (See appendix 14.2), it will be recorded as an adverse event and reported as an endpoint.

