| - Heart failure                   |                | A        |
| - chest pain                      |                | B        |
| ICD implantation                  | 6              |          |
| New onset diabetes                | 7              |          |
| Prediabetes                       | 8              |          |

Tabel 1: Clinical secondary endpoints.

A non-elective hospitalization (defined as an overnight stay, with different dates for admission and discharge) for clear symptoms of heart failure within 4 months and after long-term follow-up will be recorded. Furthermore, non-elective hospitalization (defined as an overnight stay, with different dates for admission and discharge) for chest pain will be recorded as an endpoint. Implantation of an internal cardiac defibrillator (ICD) will be recorded as an endpoint. Hospitalization for other reasons than heart failure or chest pain will not be recorded as an endpoint. Whenever a patient undergoes an elective PCI, CABG, or ICD implantation, or has a recurrent myocardial infarction or stroke, the patient is (likely to be) hospitalized. Therefore, in case of these events, the hospitalization itself will not be recorded as a separate endpoint. New onset diabetes and prediabetes, as defined by the guidelines (see Appendix 14.2) will be recorded as an endpoint. Whenever new onset diabetes is

diagnosed, patients will be treated by an endocrinologist at University Medical Center Groningen according to current guidelines. Treatment for diabetes will be additional to study treatment. Visits for treatment will be separate from study visits.

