### 14.2 Current guidelines on diagnosis of diabetes and prediabetes

#### Diabetes Mellitus

- HbA1c  $\geq 6.5\%$  or;
- Fasting glucose  $\geq 7.0$  mmol/L or;
- OGTT glucose  $\geq 11.1$  mmol/L.  
(measured at 120 minutes post glucose drink)

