#### Prediabetes

- HbA1c 5.7-6.4% or
- Fasting glucose 5.6-6.9 mmol/L (venous) (ADA) : Impaired fasting glucose (IFG);
- OGTT glucose 7.9-11.0 mmol/L (venous), WHO): Impaired glucose tolerance (IGT).  
(measured at 120 minutes post glucose drink)

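### Glycometabolic state at T0 is classified by two tests but endpoints 7 and 8 by three, and no rule keeps disease already present at T0 out of the 'new onset' count

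*Protocol*

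**What the plan says.** **At T0.** Protocol section 9.3.4.2 sorts patients during hospitalization into normal regulation, "impaired glucose regulation (impaired fasting glucose and/or impaired glucose tolerance"), and diabetes. It says that "newly detected diabetes will be based on fasting plasma glucose and glycosylated hemoglobin", following guideline definitions. The OGTT comes afterwards and is given a different purpose: "In addition, an oral glucose tolerance test (OGTT) will be performed to detect the sensitivity for glucose administration".

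**As endpoint.** Section 9.1.2 states: "New onset diabetes and prediabetes, as defined by the guidelines (see Appendix 14.2) will be recorded as an endpoint". These are classes 7 and 8 in Table 1. Appendix 14.2 joins its three diabetes criteria (HbA1c, fasting glucose, 2-hour OGTT) by 'or', so an OGTT value of 11.1 mmol/L or more is enough by itself. For prediabetes, the only criterion labelled impaired glucose tolerance is "OGTT glucose 7.9-11.0 mmol/L (venous), WHO): Impaired glucose tolerance (IGT").

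**Linking sentence.** Section 9.3.4.2 ends by saying that when diabetes or prediabetes is diagnosed under 14.2, "it will be recorded as an adverse event and reported as an endpoint". It gives no time window.

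**Schedule and entry.** Section 9.4 lists an OGTT at T0 and again at T3 (4 months). Section 9.3.4.2 describes the diabetic patients to be excluded as those with a reported diagnosis or on glucose-lowering drugs. Section 5.1 has the first dose given within 3 hours after PCI.

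**The concern.** One condition is defined by two test sets, and the narrower set is the one used at baseline. A patient with normal fasting glucose and HbA1c but a T0 OGTT in the diabetic or impaired range is normal under 9.3.4.2. The same OGTT result at T3 makes that patient an endpoint under 14.2. Entry criteria do not prevent this, because only known diabetes is excluded.

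Section 9.3.4.2 is also inconsistent in itself. It asks for a category, impaired glucose tolerance, that its two named tests cannot assign under 14.2.

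At stake are two listed clinical secondary endpoints: how many events they have, whether those events are truly new, and how large the difference between arms looks. The endpoint adjudication committee (section 10.7) must judge each endpoint as correct and complete, and here it has two rules to judge by.

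**Working it through.** The protocol gives no expected rate or power for endpoints 7 and 8, so there is no figure to reproduce. The check is a comparison of sections, followed by an illustration of size.

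**1. The sections applied to one patient** (fasting glucose and HbA1c normal, 2-hour OGTT in the diabetic range at both visits)

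| Rule | Status at T0 | Status at T3 |
|---|---|---|
| 9.3.4.2 classification | normal | not defined for T3 |
| 14.2 | diabetes | diabetes |
| 9.3.4.2 at T0, then 14.2 at T3 | normal | new onset diabetes |
| Last sentence of 9.3.4.2, applied from T0 | endpoint recorded at T0 | already counted |

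In both of the last two rows, disease present at T0 enters the endpoint count. In the last row this holds whichever test found it. An OGTT of 7.9 to 11.0 mmol/L gives the same pattern for prediabetes.

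**2. Inputs for the illustration**

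- From the protocol, section 1: a meta-analysis of metformin in persons at risk of diabetes gave a 40% relative and 6-point absolute reduction in new diabetes, over 1.8 years.
- Implied control risk: 6% / 40% = 15%, against 9% on metformin, a risk ratio (RR) of 0.60.
- Scaled to 4 months at a constant rate: p = 1 − 0.85^(0.333/1.8) = 2.96%.
- Assumed: q, the share positive only on OGTT at T0; and k, the fraction of them still positive at T3, taken as equal in both arms. The documents give neither.

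**3. Apparent risk ratio**

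Apparent RR = [qk + (1 − q) × 0.6p] / [qk + (1 − q)p]

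Example, q = 5%, k = 0.5: (0.0250 + 0.0169) / (0.0250 + 0.0282) = 0.0419 / 0.0532 = 0.79. Disease present at T0 makes up 0.0250 / 0.0532 = 47% of placebo events.

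| q | k | Placebo events | Apparent RR | Share of placebo events present at T0 |
|---|---|---|---|---|
| 5% | 0.5 | 5.3% | 0.79 | 47% |
| 5% | 1 | 7.8% | 0.86 | 64% |
| 10% | 0.5 | 7.7% | 0.86 | 65% |
| 10% | 1 | 12.7% | 0.92 | 79% |
| 15% | 0.5 | 10.0% | 0.90 | 75% |
| 15% | 1 | 17.5% | 0.94 | 86% |

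**4. Same check without scaling to 4 months** (15% against 9%, k = 1)

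Risk in each arm = q + (1 − q) × arm risk.

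- q = 5%: 13.55% / 19.25% = 0.70
- q = 10%: 18.1% / 23.5% = 0.77
- q = 20%: 27.2% / 32.0% = 0.85
- q = 30%: 36.3% / 40.5% = 0.90

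At q = 10% the two approaches give 0.86 to 0.92 and 0.77. The direction is the same, but the size depends heavily on the inputs.

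**5. Test of the equal-persistence assumption**

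Let persistence under metformin be 0.6k instead of k. Then RR = [0.6qk + (1 − q) × 0.6p] / [qk + (1 − q)p] = 0.60 exactly, with no dilution. If it is lower than 0.6k, the apparent RR falls below 0.60.

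**The case against.** **The last sentence of 9.3.4.2 may already apply 14.2 at T0.** It has no time limit, 14.2 includes the OGTT, and an OGTT is scheduled at T0. On that reading an OGTT-positive patient is diagnosed in hospital and not carried as normal until T3, and the two-test sentence is a drafting slip. This is a fair reading, but it does not remove the problem: the T0 diagnosis is then itself reported as an endpoint, so disease already present is still counted.

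**A reader might infer that the T0 OGTT shows disease before treatment.** The documents do not support that. The first dose is due within 3 hours of PCI, and section 9.4 places the OGTT only somewhere in the hospital stay. Present at T0 is as far as one can go. Section 1 adds that raised glucose in acute MI may reflect physical stress, so a T0 result need not be lasting disease.

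**A reader might infer that the effect is necessarily pulled towards 1, or that one arm is favoured.** Neither is shown. Dilution depends on equal persistence, as step 5 of the working shows, and metformin lowers glucose. Randomization balances disease present before the first dose in expectation.

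**The obvious remedy has its own flaw.** Restricting the analysis to patients negative at T0 selects on a test that may follow the first dose, and that selection could differ by arm. This stands and shapes the fix.

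**The analysis plan could settle it.** At-risk sets are often defined there, and that document is not at hand. But a conflict between two protocol sections that govern how an endpoint is recorded belongs in the protocol. It does stand that comparing the randomized arms on 14.2 status at T3 is valid. Section 2.2 frames the objective as a prevalence.

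**Conclusion.** The point holds for secondary endpoints 7 and 8 only. The current text classifies T0 by two tests and the endpoint by three, lists a T0 category that its two tests cannot assign, and has no rule for disease already present at T0. On either reading of 9.3.4.2 such disease can be counted as new onset, which overstates incidence in both arms.

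The apparent RR of 0.79 to 0.94 is an illustration, not an estimate. It rests on an assumed OGTT-only share of 5% to 15%, persistence of 50% to 100% equal in both arms, and a 1.8-year effect on diabetes taken from another population and scaled at a constant rate. It says nothing numerical about prediabetes. The figures in section 1 for diabetes among patients with an acute coronary syndrome (25% to 45% after testing) cannot stand in for the missing share: they are not limited to OGTT-only cases, and this trial excludes known diabetes.

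The primary LVEF comparison and its sample size do not depend on any of this.

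**What to change.** 1. Reconcile sections 9.1.2, 9.3.4.2 and 14.2 so that the same three criteria (HbA1c, fasting glucose, OGTT) define status at T0 and at T3.
2. State that disease meeting 14.2 at T0 is recorded as baseline status and not as a new-onset endpoint, and limit the endpoint part of the last sentence of 9.3.4.2 accordingly.
3. As the main analysis, compare all randomized patients on 14.2 status at T3, and label it as status at 4 months. This keeps the randomized comparison intact. It still includes disease carried over from T0, so it should not be described as incidence.
4. As a supportive analysis, give the comparison restricted to patients negative on all three criteria at T0. State its downsides: a smaller denominator, and possible selection on a test done after the first dose.

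The cost is wording only. Both OGTTs are already scheduled in section 9.4, so no visit or procedure is added.
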